#### Sample Size

Our sampling frame will combine the current TPS study participants across cohorts. For early childhood (0-5 years old), the planned sample size is 7,500. With an estimated response rate of 50% for the first annual THRIVE assessment (3,750 participants), and an 85% retention rate for the second annual assessment, we will have a final sample size of 3,187 children 0-5 years old over 2 years. This will provide the ability to detect a 0.08 difference in parent thriving Brief Inventory of Thriving (BIT) score and 5.5% difference in prevalence of child flourishing with a power of 85% (alpha = 0.05).

For school-age children and adolescents, the planned sample size is 4,930. With an estimated response rate of 50% for the first annual assessment (2,465 participants), and an 85% retention rate for the second annual assessment, we will have a final sample size of 2,095 children and youth 6-18 years old over 2 years. For our sample of 6- to 18-year-old children, our study will have the power to detect a 1-point difference in our main outcome of youth thriving (85% power, alpha of 0.05; BIT mean score (SD): 3.71 (0.78)).

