#### Primary Outcome Measures

Primary outcomes of TPS THRIVE are child/youth thriving measures across developmental stages. The early childhood (ages 0-5 years old) primary outcome is the National Survey of Children's Health (NSCH) (3) measure of thriving/flourishing. For school-age children and youth (aged 6-18 years old), the primary outcome is thriving score on the Brief Inventory of Thriving (BIT), a 10-item assessment of youth psychological well-being (35).

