### Data Analysis

The Biomedical Statistics and Data Science Lab also collaborates with the CRHC-DC to conceptualize and implement statistical analysis plans and facilitates interpretation of results. The Strengthening the Reporting of Observational Studies in Epidemiology (STROBE) statement (63) for observational studies and the Methodology Standards developed by the Patient-Centered Outcomes Research Institute (64) (including all cross-cutting standards) were employed in the design of the study.

For each research question, the team will develop a causal diagram (65) for the exposure-outcome relationships of interest, including a list of the predictors, confounders, mediators (i.e., measures on the causal pathway between the exposure and outcome), and potential effect modifiers of the exposure-outcome relationship. The causal diagram will be used to specify standard regression models, including linear regression for continuous outcomes, logistic regression for binary outcomes, Poisson or negative binomial regression (depending on the skewness of the outcome distribution) for counts and rates, and mixed models with a random intercept (in combination with the previously-specified types of regression models) to account for within-subject correlation (66). The included variables and their parameterization in the model (e.g., interactions or non-linear terms) are guided by clinical knowledge of the hypothesized relationship from the causal graphs. In cases where the clinical importance of a variable or subset of variables is unclear to investigators, significance tests (e.g., partial *F*-tests or likelihood ratio tests) will be used to assess significance against the reduced model (i.e., terms deemed a-priori as clinically important). In some cases, the number of variables and complexity of the model may be limited by the available sample size.

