#### Subgroup Analyses

Given the focus of TPS on building health equity in child outcomes, we will conduct subgroup analyses by child race/ethnicity, child gender identity, and family income level to determine any differential access to programs. Both unadjusted and adjusted analyses will be performed. Adjusted analyses will include key demographic variables and other variables identified as potential confounders of the relationship between the exposure and outcome measures.

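### Testing uncertain covariates for significance can leave confounding in the exposure models, and skewness is the wrong criterion for choosing Poisson or negative binomial

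*Protocol article*

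**What the plan says.** All the main statements are in the protocol article, Data Analysis.

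- **Starting point.** Each research question gets a causal diagram listing predictors, confounders, mediators and effect modifiers, from which the regression models are specified. The choice of terms rests on these diagrams: "The included variables and their parameterization in the model (e.g., interactions or non-linear terms) are guided by clinical knowledge of the hypothesized relationship from the" (the sentence ends by naming them).
- **Doubtful terms.** "In cases where the clinical importance of a variable or subset of variables is unclear to investigators, significance tests" such as partial F or likelihood ratio tests "will be used to assess significance against the reduced model (i.e., terms deemed a-priori as clinically important". No threshold is given, and no sentence says in so many words that a non-significant term is removed.
- **Counts.** "Poisson or negative binomial regression (depending on the skewness of the outcome distribution) for counts and rates". Neither overdispersion nor robust variance is mentioned.
- **Repeated measures.** The models may be extended to "mixed models with a random intercept (in combination with the previously-specified types of regression models) to account for within-subject correlation".

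Under Subgroup Analyses: "Adjusted analyses will include key demographic variables and other variables identified as potential confounders" of the exposure–outcome relationship.

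**The concern.** A partial F or likelihood ratio test measures how strongly a covariate predicts the outcome in this sample. Confounding depends also on how strongly the covariate is tied to the exposure, which the test does not measure. In fact, correlation with the exposure inflates the covariate's standard error and makes it more likely to be dropped, just when dropping it does most harm. The interval from the chosen model then takes no account of the selection. This sits badly with the causal diagram in the same paragraph. It matters because the first primary objective is to find the key factors behind thriving, and biological, social, neighbourhood and environmental factors may well be correlated with one another.

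The count rule uses the wrong property. Poisson and negative binomial differ in the variance relative to the mean, given the covariates. A skewed count need not be overdispersed, and an overdispersed count need not be very skewed. The harmful error is to fit Poisson to an overdispersed count, because the standard errors are then too small.

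**Working it through.** The plan states no figure on this point, so there is none to reproduce. The sample sizes used below agree with the Sample Size section: 4,930 × 0.50 × 0.85 = 2,095.25 and 7,500 × 0.50 × 0.85 = 3,187.5. Alpha is 0.05 there; I take it as two-sided. Confounder effects, correlations, means and dispersions are my assumptions, because the document gives none.

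**A. Testing a confounder, then dropping it**

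Set-up: standardised exposure with no effect; confounder with effect b (in SD of the outcome per SD) and correlation ρ with the exposure; residual variance 1; confounder dropped if |t| < 1.96.

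- Full model: SE of either coefficient = 1/√(n(1−ρ²)); expected t of the confounder = b√(n(1−ρ²)).
- Model without the confounder: the exposure coefficient has mean ρb and SE 1/√n, so its z statistic is centred at ρb√n.

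Example with n = 2,095, ρ = 0.5, b = 0.04: the confounder's expected t is 0.04 × √(2,095 × 0.75) = 1.59, so it is dropped about 65% of the time. If it were always dropped, z would be centred at 0.5 × 0.04 × 45.77 = 0.92 and the error would be about 15%. Averaging over keep and drop, by drawing from the large-sample joint normal distribution of the two coefficients, gives 11.8%.

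For b from 0.03 to 0.04 and n = 2,095:

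| ρ | Error with testing | Error, always adjusted | Mean bias (SD) |
|---|---|---|---|
| 0.1 | 5.2% | 5.0% | 0.001–0.002 |
| 0.3 | 6.7–7.1% | 5.0% | about 0.004 |
| 0.5 | 10.0–11.8% | 5.0% | 0.008 |
| 0.7 | 15.6–20.8% | 5.0% | 0.012–0.014 |

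At n = 3,187 and ρ = 0.5 the range is 11.4–12.7%. A finite-sample simulation (1,500 runs per cell, both sample sizes, expected t of the confounder from 1 to 2.5) agrees: up to about 8% at ρ = 0.3, 13% at 0.5 and 28% at 0.7, against 4.3–5.9% when the covariate is always kept.

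Four mutually independent confounders, each with correlation 0.3 with the exposure (joint correlation √(4 × 0.3²) = 0.6), n = 2,095: testing each separately gives 19.9% at b = 0.03 and 22.4% at b = 0.04, with bias about 0.02 SD. Testing the four together gives about 24–26%. Full adjustment gives 5%.

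**B. Skewness against dispersion**

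- Poisson: skewness = 1/√μ, variance/mean = 1.
- Negative binomial with size k: p = k/(k+μ), skewness = (2−p)/√(k(1−p)), variance/mean = 1 + μ/k.
- Error of a nominal 5% test fitted as Poisson = 2(1 − Φ(1.96/√(variance/mean))).

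| Outcome | Skewness | Variance/mean | Error as Poisson |
|---|---|---|---|
| Poisson, μ = 0.5 | 1.41 | 1 | 5% |
| Poisson, μ = 5 | 0.45 | 1 | 5% |
| Negative binomial, μ = 20, k = 10 | 0.65 | 3 | 25.8% |
| Negative binomial, μ = 50, k = 20 | 0.45 | 3.5 | 29.5% |

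For the third row, p = 1/3, skewness = 1.667/√6.667 = 0.65, and a Poisson standard error is 1/√3 = 0.58 of the true one. The second and fourth rows have the same skewness, so no skewness cut-off can separate them.

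**The case against.** The strongest reply is that testing is a fallback. The diagram comes first, terms judged important a priori stay in the reduced model, and Subgroup Analyses says that adjusted analyses include identified potential confounders. The preceding sentence also mentions interactions and non-linear terms, for which testing is reasonable. Keep or drop is inferred, and thresholds and dispersion checks may be in an analysis plan that is not shown.

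Much of this stands. It rules out the reading that every confounder is put to a significance test. It does not clear the rule. The exempt set consists of terms deemed important in advance, so a variable drawn as a possible confounder but of unclear importance falls in the tested set. The sentence about tests names variables, and comparison with a reduced model has little other practical use than to decide whether terms stay. The sentence under Subgroup Analyses does not say that it overrides the earlier one. Both rules are stated methods, not details left for later.

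A reader might also infer that the two rules always give standard errors that are too small or residual confounding. They do not. At correlations of 0.1–0.3 testing one confounder costs little, and the absolute bias is small at these sample sizes. Choosing negative binomial for a skewed true Poisson count is largely harmless.

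Nor does the count rule reach the main results. For ages 6–18 "the primary outcome is thriving score on the Brief Inventory of Thriving (BIT", a continuous score, and for ages 0–5 flourishing is planned as a prevalence ("5.5% difference in prevalence of child flourishing with a power of 85% (alpha = 0.05"). The listed secondary outcomes name no count. Counts could arise from the health service encounters under Secondary Data Collection. In repeated counts the random intercept may absorb between-subject overdispersion, though not in counts taken at a single time point.

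**Conclusion.** The point holds in conditional form. Significance testing of uncertain covariates can leave residual confounding and understate uncertainty when a weak confounder is clearly correlated with the exposure. Under the assumed effects of 0.03–0.04 SD at N = 2,095, the error is roughly double the nominal level for one confounder at correlation 0.5 and about four times nominal for four at joint correlation 0.6, with bias of about 0.01–0.02 SD. These sizes rest on assumed correlations and effects, and on reading the test as a keep-or-drop rule.

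Skewness is the wrong criterion for the count model whatever the inputs. The 26% figure is an illustration: it matches no measure in the protocol and assumes that a skewness of 0.65 would lead to Poisson, for which no cut-off is given. This half is the lesser one because it concerns count outcomes only. Neither half invalidates the design; both should be corrected before the models are fitted.

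**What to change.** Change two sentences in Data Analysis.

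1. Keep every potential confounder identified in the causal diagram, including those of uncertain importance, whatever its p-value. Limit significance tests to non-linear or interaction terms and label those results exploratory. This would also bring the section into line with Subgroup Analyses.
2. Choose between Poisson and negative binomial by dispersion given the covariates, or use negative binomial, or Poisson with robust variance, by default.

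The cost is a few extra degrees of freedom, trivial with 2,095 to 3,187 children. The section already notes that sample size may limit model complexity. Where it does in small subsets, the set of covariates can be shortened from the diagram instead of by p-value.

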#### Subgroup Analyses

Given the focus of TPS on building health equity in child outcomes, we will conduct subgroup analyses by child race/ethnicity, child gender identity, and family income level to determine any differential access to programs. Both unadjusted and adjusted analyses will be performed. Adjusted analyses will include key demographic variables and other variables identified as potential confounders of the relationship between the exposure and outcome measures.

#### Missing Data and Potential Bias in Attrition

Given the pragmatic nature of these studies, missing data and attrition can be expected. The degree of missingness will be described for all variables, and summaries of the other variables will be used to describe differences between observations with missing and non-missing values for key variables to assess the likelihood of missing at random. For variables that are deemed to be missing at random, imputation or multiple imputation may be used (depending on the percentage of missingness) to improve precision. Lost to follow-up will be described consistent with STROBE guidelines.

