### Strengths and Limitations

Strengths of TPS THRIVE include its grounding in a comprehensive, community-informed conceptualization of childhood thriving and its asset-based approaches in building on the strengths of families and neighborhoods in supporting childhood thriving. This transdisciplinary collaboration integrates experts in pediatrics, developmental science, education, health services research, community health, public health, social work, biostatistics, epidemiology, behavioral health, engineering, and biological and environmental science along with community organizations in an innovative community-partnered research model. By integrating community organizations and members, this study builds on positive practices already present in our community, identifying interventions that have community relevance and contextual validity.

Limitations of this study include self-report bias of survey data, selection bias, and lack of randomized, control groups for some of the cohort intervention studies. Secondary data and direct assessments will be used when available to supplement self-reported survey data. Propensity score matching to account for group differences will be used when randomized comparison groups are unavailable. Different sample inclusion/exclusion criteria may make it difficult to compare children across cohorts over time.

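### The missing-data rule allows imputation only where data are judged missing at random, on comparisons that cannot show this, and it permits single imputation, which understates standard errors

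*Protocol article*

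**What the plan says.** The protocol article, under Missing Data and Potential Bias in Attrition, sets out a sequence. Missingness is described for every variable. Records with and without values on key variables are compared on the other variables, to judge how likely MAR is. Then: "For variables that are deemed to be missing at random, imputation or multiple imputation may be used (depending on the percentage of missingness"). The stated aim is better precision; bias is not mentioned. No percentage is given at which the method changes, and nothing is said about variables judged not MAR. Loss to follow-up is to be described.

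Under Sample Size the article expects "an 85% retention rate for the second annual assessment", that is, 15% loss between the two waves.

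Under Study Comparison Groups, change over time is examined with paired t-tests and McNemar tests, alongside adjusted regression models. Data Analysis adds random-intercept mixed models, for the stated purpose of handling within-subject correlation.

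**The concern.** The rule sorts variables by a judgement that the proposed evidence cannot support. It can also work the wrong way round. If records with missing values differ visibly from the rest, an analyst may decline to call the variable MAR and so not impute it. Yet those observed differences are the information that an imputation model should use.

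Setting imputation against multiple imputation, with the choice depending on the amount missing, means that the plain form is single imputation. Analysed as if real, singly imputed values give standard errors that are too small and tests that reject too often. The stated aim of improving precision makes this worse, because single imputation mostly improves the precision that is reported rather than the precision that is achieved.

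At stake are the validity of intervals and tests for thriving scores and prevalence, and whether the wave-to-wave comparisons use the available information on families who drop out.

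**Working it through.** **Expected loss.** From Sample Size: 7,500 × 0.50 × 0.85 = 3,187.5 and 4,930 × 0.50 × 0.85 = 2,095.25. Both stated final sizes (3,187 and 2,095) reproduce. The second-wave loss among first-wave responders is 1 − 0.85 = 15%.

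**The MAR judgement.** Let R mark whether an outcome Y is missing, and let X be the other, observed variables.
- MCAR: the chance of R depends on neither X nor Y.
- MAR: it depends only on what is observed.
- MNAR: given what is observed, it still depends on the unseen Y.

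Comparing X between the two sets of records shows how R varies with X. If it varies, MCAR is contradicted. What separates MAR from MNAR is whether R depends on Y after X is taken into account, and Y is unseen where R marks it missing. A MAR mechanism and an MNAR mechanism can give identical differences in X. So differences do not count against MAR, and their absence does not establish it.

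**Single imputation.** Inputs: share missing m; correlation r between the outcome and the covariate used to impute, assumed 0.3 to 0.5 because the article gives none; outcome MCAR; outcome variance set to 1. For a mean over n records imputed by regression:
- true variance × n = r² + (1 − r²)/(1 − m)
- reported variance × n = r² + (1 − m)(1 − r²)
- actual error of a nominal 5% test = 2Φ(−1.96 × √(reported/true))

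If random residual noise is added to each imputed value, the reported variance becomes 1 and the true variance rises by m(1 − r²).

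At m = 0.15:
- r = 0.5, no noise: true 0.25 + 0.75/0.85 = 1.132; reported 0.25 + 0.85 × 0.75 = 0.8875; error 8.3%. With noise: true 1.132 + 0.1125 = 1.245; error 7.9%.
- r = 0.3, no noise: true 0.09 + 0.91/0.85 = 1.161; reported 0.09 + 0.85 × 0.91 = 0.8635; error 9.1%. With noise: true 1.161 + 0.1365 = 1.297; error 8.5%.

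On precision, at r = 0.5 the complete cases alone have variance 1/0.85 = 1.176. Regression imputation truly lowers this only to 1.132, but reports 0.8875, which is below the value of 1 that complete data would give.

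| Missing | Simulated error, n = 2,000 | Formula above |
|---|---|---|
| 2-5% | about 5-6.5% | 5.3-6.1% |
| 15% | 8-9% | 7.9-9.1% |
| 30% | 12-16% | 11.5-15.6% |
| 50% | 17-27% | 17.9-29.5% |

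The two agree closely up to 30% missing. At 50% the upper end depends more on the method and the correlation. A separate simulation with n = 3,187 and r = 0.5 gave 95% intervals that covered about 90-92% at 15% missing and 68-80% at 50%, the lower ends coming from filling in the mean.

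**The case against.** Four points count on the other side.

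- **The wording is soft.** The article assesses a likelihood and says that imputation may be used. Describing records by missingness is ordinary good practice. This stands for the description, but not for making imputation conditional on the result.
- **Single imputation may be meant only for small amounts.** That is the natural reading of a choice tied to the percentage missing, and at 2-5% the inflation is minor. Nothing says that a primary outcome would be singly imputed. But no threshold is stated, so heavier use is not excluded.
- **Mixed models are already planned.** Fitted to all available waves, they handle missing outcomes under MAR given the variables in the model. The article adopts them only for within-subject correlation, and they do not by themselves deal with missing covariates.
- **An analysis plan may say more.** It could replace this rule, but the points above concern what the article states.

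Two stronger readings are tempting. A reader might infer that variables judged not MAR go to complete-case analysis. The article does not say so, although paired tests use complete pairs by default.

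A reader might also infer that the 50% non-response at the first assessment goes uncorrected and biases the results. The article states "With an estimated response rate of 50% for the first annual THRIVE assessment (3,750 participants") and "Our sampling frame will combine the current TPS study participants across cohorts", and it concedes the problem: "Limitations of this study include self-report bias of survey data, selection bias". But weighting for non-response is commonly left to an analysis plan, and nothing shows that race, income or neighborhood is held for non-responders. The article gives no responder/non-responder gap either. With 50% non-response, assumed gaps of 0.1, 0.2 and 0.3 SD would shift a mean by 0.5 × gap × 0.78 = 0.039, 0.078 and 0.117. It would be wrong to read 0.078 against the stated detectable 0.08: the SD of 0.78 is given for ages 6-18 and the 0.08 for parents of children aged 0-5. A shift common to both groups or both waves also cancels in a contrast.

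**Conclusion.** The point holds for the stated rule and should be corrected. The MAR judgement cannot be made from the comparisons described, and that conclusion needs no numerical assumption. Single imputation is permitted without a limit. At the 15% second-wave loss that the plan itself expects, it would run a nominal 5% test at about 8-9%. The effect is slight at 2-5% missing and serious at 50% (17-27% simulated). These figures assume an outcome MCAR, a covariate correlation of 0.3 to 0.5, and imputed values analysed as observed. They show what the rule allows, not what the analysts will necessarily do. No claim is made about the size of bias from first-assessment non-response, because the article does not give the figures needed.

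**What to change.** 1. Delete the condition that a variable must be judged MAR before it is imputed. Keep the description of missingness, and use it to choose auxiliary variables.
2. Delete single imputation as an option.
3. For change over time, make one of two approaches the default, in place of paired t-tests and McNemar tests on complete pairs: multiple imputation with auxiliary variables, including those found to predict missingness, or the planned mixed models fitted to all available waves. Use multiple imputation where covariates are missing.
4. Add a delta-shift sensitivity analysis for the primary outcomes (child flourishing at 0-5 years, BIT score at 6-18 years). It moves the imputed values away from their MAR prediction over a stated range and reports where the conclusion changes.
5. Optionally, weight by the inverse probability of retention as a sensitivity analysis for the 15% second-wave attrition. First-wave data supply the predictors.

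The cost is analysis programming only. No extra data collection or change to the sample size is needed.
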